### Clinical follow-up procedure

Patients are discharged home within 2 days after the index procedure. Antiarrhythmic medication is discontinued after the ablation procedure. Follow-up of study patients is implemented as outlined in Table 2. All patients undergo physical examination, 12-lead ECG and echocardiography before and the next day after the procedure (note: only bedside echocardiography is performed after the procedure, in order to control for pericardial effusion). After discharge, patients have an outpatient visit at 3 months and at 12 months after the index procedure. During these outpatient visits, patients will be assessed for recurrence of palpitations (medical history), in addition to a physical examination and a 12-lead ECG. Additional outpatient visits during the 12-month follow-up period are scheduled only in the case of recurrence of symptoms (symptom-based follow-up appointments). In these cases, a detailed medical history and a 12-lead ECG will be taken, and the following additional examinations can also be performed (if necessary) in order to document the clinical arrhythmia: Holter monitoring (up to 3 weeks) and/or trans-telephonic event recorder (CardioMemo). In the case of recurrence, a redo electrophysiology study can be scheduled. An event qualifies as recurrence of clinical arrhythmia if the patient experiences identical complaints to those before the ablation procedure, and the same type of narrow-complex tachycardia is recorded with any of the following: 12-lead ECG, Holter monitor or trans-telephonic event recorder (CardioMemo). In addition, a recurrence is also identified in case the same type of clinical arrhythmia can be induced during a potential redo electrophysiology study, that was indicated due to recurrent palpitations. The occurrence of (serious) adverse events will be assessed and followed-up during the procedure, before discharge, and at 3 and 12 months post discharge (additional follow-up appointments can also be scheduled if necessary). Echocardiography is done in case follow-up of pericardial effusion/tamponade is necessary, chest X-ray is done to follow-up possible phrenic nerve damage and vascular ultrasound is done if vascular access complications require it.

**Table 2 Tab2:** Follow-up design of the COBRA-PATH study

Type of clinical examination	Before the index procedure	1 day after the index procedure	3 months after the index procedure (outpatient visit)	12 months after the index procedure (outpatient visit)
Physical examination/history^a^	+	+	+	+
12-lead surface electrocardiogram^a^	+	+	+	+
Echocardiography	+	+ (bedside echo)	**–**	–
24-h (or longer-term) Holter monitoring^a^	If available	–	In case necessary to detect possible recurrence^b^	In case necessary to detect possible recurrence^b^
Trans-telephonic event recorder (CardioMemo)	If available	–	In case necessary to detect possible recurrence^b^	In case necessary to detect possible recurrence^b^

*COBRA-PATH* Contact-Force-Sensing-Based Radiofrequency Catheter Ablation in Paroxysmal Supraventricular Tachycardias

^a^These examinations can also be scheduled any time during the 12-month follow-up period in the case that the patient experiences recurrence of symptoms (symptom-based follow-up appointment)

^b^Decision to perform these examinations will be made jointly by the treating cardiologist and the study investigators

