### Study groups and randomization process

Consecutive patients on the waiting/referral list for PSVT ablations (referred to our tertiary center by other hospitals) will be screened for eligibility by dedicated study coordinators. When they meet the inclusion criteria, the patients will be enrolled in the study (as depicted in the flowchart for the study; see Fig. 1). After enrolment, patients will be allocated a unique study subject number in chronologically ascending order. Subsequently, they will be randomized to two treatment arms: the “CF-sensing” arm, ablation with a CF-sensing ablation catheter; and the “conventional” arm, standard ablation approach using a conventional (noncontact force-sensing) ablation catheter. Randomization will be performed by a computer-generated program (ALEA) based on a block randomization protocol using a block size factor of four. Randomization into the two treatment arms will be carried out with a 1:1 randomization ratio (50% probability for both treatment arms). The process of randomization will follow the general concepts of allocation concealment by incorporating the following prerequisites into the conduct of randomization: the EP specialists performing the ablation procedures do not have knowledge on the method of randomization utilized in the study; the EP specialists performing the ablation procedures do not keep a record of the results of randomization during previous ablation procedures; withdrawal from enrolment and randomization after the initial screening process and the subsequent EP study (that was positive for AVNRT or WPW-AVRT) must be explained thoroughly in the official clinical report by the treating specialist; the person in charge of the randomization process will not be the treating physician and neither will he/she be involved in the patient selection process; and the person in charge of the randomization will be contacted (over the telephone) by the treating specialist after the diagnostic part of the procedure has been completed. Stratification for study specific factors will not be conducted. The study will be performed in an open-label fashion: neither the patient nor the electrophysiologist (performing the procedure) will be blinded for the specific type of procedure.

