### Statistical analysis

The number of radiofrequency applications during the ablation procedures of AVNRT and WPW-AVRT (primary study endpoints), as well as other continuous procedural parameters from the group of secondary study endpoints (such as total procedural duration, fluoroscopy time and overall duration of RF applications), will be expressed as mean ± SD or median (interquartile range) depending on their distributions, and statistical analysis of these variables will be conducted using either the two-sample *t* test or the Mann–Whitney test, again depending on the underlying distribution of the data.

The recurrence rate of PSVT at 1 year (as an indicator of long-term success rate of the index procedure), as well as the acute success rate and the major/minor complication rates of the index procedures (secondary study endpoints), will be presented as absolute and relative frequencies. The associations between treatment and these secondary endpoints will be analyzed with the chi-squared test or with Fischer’s exact test, as appropriate. Moreover, logistic regression will be performed to examine these associations and will, if needed, be adjusted for unbalanced baseline characteristics. Freedom from PSVT recurrence will be determined with Kaplan–Meier analysis, and differences in recurrence-free survival rates will be evaluated with the log-rank test. A *p* value of 0.05 will be considered significant for all statistical determinations, and all reported *p*-values will be based on two-sided tests.

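### The recording route to a recurrence demands complaints identical to those before ablation, while the redo-study route demands only recurrent palpitations, so some documented relapses count only if an optional redo study is done

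*Protocol article*

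**What the plan says.** Recurrence is defined in the Protocol article, Clinical follow-up procedure, by two routes.

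- **Recording route.** The symptom condition is "An event qualifies as recurrence of clinical arrhythmia if the patient experiences identical complaints to those before the ablation procedure". It is joined to a rhythm condition: "and the same type of narrow-complex tachycardia is recorded with any of the following", followed by 12-lead ECG, Holter monitor and event recorder.
- **Redo route.** This is offered as an additional way to qualify: "a recurrence is also identified in case the same type of clinical arrhythmia can be induced during a potential redo electrophysiology study". Its symptom condition concerns the reason for the redo study: "that was indicated due to recurrent palpitations".

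The redo study is optional: "In the case of recurrence, a redo electrophysiology study can be scheduled".

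The Statistical analysis section uses the result as a secondary endpoint, "The recurrence rate of PSVT at 1 year (as an indicator of long-term success rate of the index procedure". It is compared by chi-squared or Fisher test and by logistic regression. Recurrence-free survival is analysed by Kaplan-Meier and log-rank.

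On masking, Study groups and randomization process states that "neither the patient nor the electrophysiologist (performing the procedure) will be blinded for the specific type of procedure".

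**The concern.** Both routes ask for symptoms and for objective proof of the same arrhythmia. Only the recording route also requires the complaints to match those before ablation. Nothing in the article says what identical means, treats the two symptom terms as equivalent, or says how to score a recorded tachycardia with changed complaints when no redo study follows.

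The complaints described under Study population have several parts: rapid palpitations of sudden onset and end, often with neck pulsation or dizziness. A relapse can return some of these and not others, for example as shorter or milder attacks. Applied as written, the rule then scores a documented return of the treated tachycardia as long-term success.

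Two things can decide whether such a patient counts: a judgement of whether the complaints are identical, which rests on the account of an unblinded patient, and whether an optional redo study is done. Neither is an effect of the catheter on recurrence.

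**Working it through.** **1. The rule applied to three patients.** All had palpitations with dizziness before ablation for AVNRT.

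| Patient | Complaints after ablation | Objective finding | Recording route | Redo route | Scored |
|---|---|---|---|---|---|
| A | Same as before | AVNRT on ECG | Met | Not needed | Recurrence |
| B | Milder palpitations, no dizziness | AVNRT on ECG, no redo | Not met (not identical) | Not available | No recurrence |
| C | As B | AVNRT on ECG, and AVNRT induced at redo | Not met | Met | Recurrence |

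B and C have the same symptoms and the same recording. They differ only in whether the optional study was done. A and C show that the routes agree in other respects.

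**2. The plan's own number of patients.** This is needed only for scale. Inputs from Sample size calculation: log-scale means 1.39 and 1.043 (difference 0.347), SD 0.59, two-sided alpha 5%, power 80%.

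- n per arm = 2 × (1.960 + 0.842)² × 0.59² / 0.347² = 45.4, rounded up to 46; total 92.
- 92 × 1.15 = 105.8, given as 106; 106 / 0.95 = 111.6, given as 112.

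The stated figures reproduce. They concern the number of RF applications and do not depend on the recurrence definition.

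**3. Expected recurrences.** Background gives about 5% (AVNRT) and about 8% (WPW-AVRT).

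- Whole trial: 112 × 0.05 = 5.6 to 112 × 0.08 = 9.0.
- Per arm of 56: 2.8 to 4.5.

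**4. Events lost.** Let s be the share of recorded relapses with non-identical complaints, and u the share of those that have a redo study that induces the arrhythmia. Events counted = true events × (1 − s(1 − u)). The article gives neither s nor u, so the values here are assumptions. At 8% in 56 patients with u = 0:

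| s (assumed) | Expected events counted, of 4.48 |
|---|---|
| 10% | 4.48 × 0.90 = 4.0 |
| 25% | 4.48 × 0.75 = 3.4 |
| 50% | 4.48 × 0.50 = 2.2 |

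**5. An uneven case, for illustration only.** Take s = 40%, with u = 80% in one arm and 30% in the other. A true 8% in both arms is scored as 0.08 × (1 − 0.4 × 0.2) = 7.4% and 0.08 × (1 − 0.4 × 0.7) = 5.8%, a ratio of 0.78. In events this is 56 × 0.0736 = 4.1 versus 56 × 0.0576 = 3.2, a difference of 0.9.

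**6. Effect on a test.** Fisher's exact test with 56 per arm: 4 versus 4 gives p = 1.0, and 4 versus 2 gives p = 0.68. Even 5 versus 0 gives p = 0.057. Reclassifying one or two events would rarely move a result across 0.05.

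**The case against.** The strongest reply is that the word identical is being read too strictly. The same section describes symptoms after ablation in several loose ways and defines none of them. For symptomatic patients the entry complaint is palpitations, with dizziness or neck pulsation as accompaniments. An assessor could take the clause to mean that the same kind of complaint is back. Patient B would then be a recurrence and the difference would vanish. That reading is plausible, and most relapses in symptomatic patients would meet both wordings. But it is not what the sentence says, and the article does nothing to make assessors choose it. Two assessors could score B differently, each with support in the text.

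A reader might infer three stronger things that the documents do not support.

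- *The redo route accepts symptoms alone.* It does not. It also requires induction of the same arrhythmia, which parallels the recording.
- *The two routes give conflicting verdicts.* They are alternatives, so a patient who meets either one counts. The gap concerns the patient with a recording, changed complaints and no redo study.
- *Any recorded tachycardia ought to count, whatever the symptoms.* An endpoint of symptomatic, documented recurrence is a legitimate choice and fits a follow-up in which extra visits are prompted by symptoms. The short endpoint label in Statistical analysis does not contradict it.

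It is also fair to say that the stakes are limited. The endpoint is secondary, and the Abstract already concedes that better success rates may not be demonstrable. That weakens any argument from lost power. It does not remove the interest in a correct recurrence estimate.

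**Conclusion.** The point holds as an inconsistency in a stated endpoint definition. Followed as written, the recording route can score an objectively documented, symptomatic return of the treated tachycardia as long-term success, and an optional redo study can reverse that score.

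The effect is an undercount in a subset of unknown size. With about 6 to 9 events expected in all, one or two reclassified events would be visible in the recurrence rate and the Kaplan-Meier curves, but would rarely change a test. The primary outcome and the sample size are not affected.

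A reader might go further and conclude that the recurrence rate is understated, or that the arms will differ for this reason. The documents do not show either. Undercounting needs relapses with changed complaints that are recorded, have no redo study and are scored literally. A difference between arms also needs the judgement of complaints or the uptake of redo studies to differ by arm. The open-label design makes that possible, but the article gives no figure for it. The shares used in the working are assumptions.

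The conclusion concerns patients who had symptoms before ablation. Study population also admits patients with a manifest accessory pathway who never had palpitations. They have no earlier complaint to match, which is a separate matter.

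**What to change.** In Clinical follow-up procedure, replace the identical-complaints condition in the recording route with the symptom condition already used for the redo route. A recurrence is then recurrent palpitations plus either a recording or an induction of the same type of tachycardia. Patients A, B and C would all count, and an optional study would no longer decide the score of a relapse that is already documented. Record whether the complaints resemble the earlier ones as a descriptive item.

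The cost is one sentence. No visit, test or analysis is added, because the recordings are already collected. The small downside is that the observed recurrence rate may be slightly higher. Counting recordings regardless of symptoms would be a different design choice and is not needed to remove the inconsistency.

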Patients with evidence of a manifest accessory pathway (i.e. pre-excitation on surface ECG and/or findings supporting anterograde conduction over an accessory pathway during standard EP study) who also present with documented narrow (or wide)-complex tachycardia, which proves to be orthodromic (or antidromic) AVRT by the EP study. (Note: antidromic AVRT is a quite rare entity.)Patients presenting with documented orthodromic AVRT using a concealed bypass tract (accessory pathway conducting only in the retrograde direction).Patients who possess a manifest accessory pathway (pre-excitation on ECG and/or evidence for anterograde conduction during EP study; similar to group 1) but have never experienced palpitations and have no prior documentation of tachycardia. In these patients, RF ablation of the accessory pathway will be offered for those individuals who possess a manifest accessory pathway with an anterograde ERP less than 240 ms, and/or for whom EP study identifies a reproducibly inducible AVRT. These patients can be enrolled in our study, even if no tachycardia had been experienced or documented in the past.

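### The recurrence definition does not fit two enrolled groups: never-symptomatic pre-excitation, and wide-complex AVRT on the recording route

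*Protocol article*

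**What the plan says.** **Who is enrolled** (Protocol article, Study population). The WPW-AVRT label covers three groups. Group 1 has a manifest pathway with "documented narrow (or wide)-complex tachycardia, which proves to be orthodromic (or antidromic) AVRT by the EP study"; the article adds that the antidromic form is rare. Group 2 has orthodromic AVRT over a concealed pathway. Group 3 has a manifest pathway, "but have never experienced palpitations and have no prior documentation of tachycardia". Group 3 patients are offered ablation for a short anterograde refractory period, for reproducibly inducible AVRT, or for both, and are expressly allowed into the trial.

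**What counts as recurrence** (Clinical follow-up procedure). There are two routes.
- Recording route: "An event qualifies as recurrence of clinical arrhythmia if the patient experiences identical complaints to those before the ablation procedure" and, in addition, "the same type of narrow-complex tachycardia is recorded with any of the following: 12-lead ECG, Holter monitor or trans-telephonic event recorder".
- Redo route: the "same type of clinical arrhythmia can be induced during a potential redo electrophysiology study, that was indicated due to recurrent palpitations". The redo study is optional: "In the case of recurrence, a redo electrophysiology study can be scheduled".

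**How it is used** (Primary and secondary outcome parameters; Statistical analysis). Long-term procedural success is a secondary outcome, and one-year PSVT recurrence is its indicator. It is analysed by chi-squared or Fisher's exact test, logistic regression, Kaplan–Meier curves and a log-rank test.

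**The concern.** Both routes look back to the patient's state before ablation. The recording route asks for the same complaints and the same type of narrow-complex tachycardia. The redo route asks for palpitations that recur and the same clinical arrhythmia. Group 3 had no complaints, no palpitations and no documented tachycardia, so there is nothing to compare with. A wide-complex tachycardia fails the recording route on QRS width alone, even though the same article admits patients with it.

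This is not detail left to a fuller document. The rule is stated in full, and applied literally it gives the wrong answer for patients whom the article chooses to enrol. Someone who cannot meet the definition stays in the denominator and counts as a long-term success. At stake are the reported one-year success rate and the number of events behind the survival comparison.

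**Working it through.** **Step 1. Each route against each enrolled group**

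| Group | Recording route | Redo route |
|---|---|---|
| AVNRT | Open | Open |
| Group 1, orthodromic | Open | Open |
| Group 1, antidromic (wide complex) | Closed by the narrow-complex condition | Open, if palpitations lead to a redo study and the AVRT is induced |
| Group 2, concealed pathway | Open | Open |
| Group 3, AVRT induced at the index study | Closed: no prior complaints to match | Open only if *recurrent* is read as repeated new palpitations, and *clinical arrhythmia* as the AVRT induced at the index study |
| Group 3, short refractory period only | Closed | No earlier tachycardia to be the same as |

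**Step 2. The base of 112**

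No figure in the article depends on the recurrence definition. The sample size rests on the number of RF applications, and it reproduces:
- Log-scale difference 1.39 × 0.25 = 0.3475; SD 0.59; two-sided 5%; power 80%.
- n per arm = 2 × (1.96 + 0.8416)² × 0.59² / 0.3475² = 45.3, rounded up to 46, so 92 in total.
- 92 × 1.15 = 105.8, about 106. Then 106 / 0.95 = 111.6, about 112.

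**Step 3. Expected recurrences**

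The Background gives about 5% for AVNRT and about 8% for WPW-AVRT.
- 112 × 0.05 = 5.6
- 112 × 0.08 = 9.0

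**Step 4. Events that could not be counted in group 3**

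Two assumptions are needed: that group 3 makes up 10–20% of patients (no share is given), and that the 8% rate applies to it.
- 10%: 11.2 × 0.08 = 0.9 events
- 20%: 22.4 × 0.08 = 1.8 events

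As a share of all events:
- Everyone else at 8%: 0.9 / 9.0 = 10% and 1.8 / 9.0 = 20%.
- Everyone else at 5%: 0.9 / (0.9 + 100.8 × 0.05) = 0.9 / 5.9 = 15%, and 1.8 / (1.8 + 89.6 × 0.05) = 1.8 / 6.3 = 29%.

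On the 92 patients before allowances, the same sums give 4.6 to 7.4 events expected and 0.7 to 1.5 lost.

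No figure is put on the antidromic group. Its share is not given, it is described as rare, and the redo route remains available to it.

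**The case against.** Four objections deserve an answer.

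**The exclusion is not absolute.** A reader might infer that no group 3 or antidromic recurrence can ever be counted. The text does not support that. Antidromic AVRT can count through a redo study without strain. A group 3 patient with AVRT induced at the index study, who later has palpitations and the same AVRT at a redo study, could be counted if *recurrent* means repeated. The stricter meaning is the more natural one, because the same section has patients assessed for recurrence of palpitations they had before. This objection limits the point but does not remove it.

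**Returned pre-excitation is not PSVT.** A reader might go further and call silent return of pre-excitation on the 3- or 12-month ECG a missed recurrence, since the ablation section treats re-conduction over the pathway as a reason for further applications. That rule governs the index procedure. The analysed endpoint is PSVT recurrence, and a patient with returned pre-excitation but no tachycardia is correctly PSVT-free. Counting it would change the endpoint. This objection stands, so the finding belongs in a separate outcome.

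**Discretionary recording is a different matter.** Table 2 says of Holter and event recording: "Decision to perform these examinations will be made jointly by the treating cardiologist and the study investigators". In an open-label trial a reader might infer that detection differs by arm. The text shows the opportunity, not that it happens, and nothing in the article gives it a size. It does not bear on whether the definition fits the population.

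**Little turns on it.** The endpoint is secondary, the definition is the same in both arms, and the abstract concedes that an improvement in success rates may not be demonstrable. With 56 per arm and an assumed halving from 8% to 4%, a two-proportion comparison has about 14% power, and about 12% if 20% of events go uncounted. The comparison is uninformative either way. This stands, and it is why the effect falls on the reported rate more than on the test.

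**Conclusion.** The point holds in a limited form. The recurrence definition and the admitted population do not match. Never-symptomatic patients cannot qualify by recording and qualify by redo study only on a loose reading, so they are event-free almost by construction. Recorded wide-complex AVRT fails the recording route but can still count through a redo study.

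The effect is an understated recurrence rate, and so an overstated long-term success rate, in both arms. The size is about 1 to 2 events out of roughly 6 to 9. That rests on an assumed 10–20% share for group 3 and on an 8% rate that the article does not show to apply to patients without symptoms. The percentage loss of 10–29% is no firmer than those assumptions, and its upper end also needs nearly all other patients to recur at the AVNRT rate.

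The definition is worth correcting, but it does not threaten the trial. The primary endpoint and the sample size do not depend on it.

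**What to change.** Reconcile Study population with Clinical follow-up procedure:

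1. For group 3, count as recurrence any AVRT that is documented or induced during follow-up, without the condition of matching complaints or recurrent palpitations.
2. For the other patients, replace the condition "and the same type of narrow-complex tachycardia is recorded with any of the following" by one that asks for the same tachycardia mechanism, narrow or wide complex.
3. Report return of pre-excitation on the scheduled 3- and 12-month ECGs in manifest-pathway patients as a separate long-term procedural outcome or sensitivity analysis, not as PSVT recurrence.
4. Report the number of group 3 and antidromic patients per arm, so that the size of the problem is visible.

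The cost is one paragraph of endpoint definition and one or two table rows. No visit or examination is added, since the ECGs are already scheduled. The reported recurrence rate may be slightly higher. One limit remains: extra visits and longer recordings are prompted by symptoms, so the change lets an AVRT in a never-symptomatic patient count once it is found but does not make it more likely to be found.

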### Study population

All patients without structural heart disease being referred to participating centers for standard electrophysiological study either because of pre-excitation detected on 12-lead surface ECG or because of palpitations associated with documented narrow-complex tachycardia (or clinical signs highly suggestive of the palpitation being associated with PSVT: sudden onset and termination of rapid and regular palpitations—the palpitations can usually be terminated with Valsalva maneuver or carotid sinus massage) will be eligible. In addition, in order to be eligible for participating in the trial, an electrophysiology study must identify AVNRT or WPW-AVRT (see clarification in the following) as the underlying arrhythmia mechanism [26–29]. In order to be included in the study, a subject must meet all of the following criteria:
Referral for electrophysiology study because of pre-excitation on 12-lead surface ECG and/or documented (or suspected) symptomatic PSVT: palpitations associated with narrow-complex tachycardia (≥ 1 episode) documented by a 12-lead electrogram, Holter monitoring, trans-telephonic event recorder, telemetry strip or implanted device (implantable loop recorder, pacemaker) within 12 months prior to referral to EPS; or frequent symptoms of palpitation (within 12 months prior to referral) associated with clinical signs highly suggestive of PSVT—sudden onset and termination of rapid (and regular) palpitations usually accompanied with neck pulsation and/or dizziness, termination with Valsalva maneuver or carotid sinus massage, and no evidence for an underlying structural heart diseaseIdentification of AVNRT or WPW-AVRT (with manifest or concealed accessory pathway) during standard EP studyVerbal consent to continue with ablation therapy after the diagnostic steps of the EPS identified the aforementioned arrhythmia mechanisms, and after the patient received sufficient information about the benefits and potential risks of the ablative treatment of the individual arrhythmia substrateInformed written consent to being included in the study

A potential subject who meets any of the following criteria will be excluded from participating in this study:
Evidence of structural heart disease and/or myocardial ischemiaPregnancy (and lack of exclusion of potential pregnancy)Age below 18 years

In this study protocol, we use the term WPW-AVRT to describe the following disease entities:

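### The recurrence definition omits telemetry strips and implanted devices, which are accepted at entry, so a symptomatic recurrence recorded only that way is not counted or is counted late (minor; secondary endpoints only)

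*Protocol article*

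**What the plan says.** **Entry (Protocol article, Study population).** One route into the trial is palpitations with narrow-complex tachycardia "documented by a 12-lead electrogram, Holter monitoring, trans-telephonic event recorder, telemetry strip or implanted device (implantable loop recorder, pacemaker) within 12 months prior". That is five sources. Patients who already carry a loop recorder or pacemaker are named here, and the exclusion criteria do not remove them.

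**Recurrence (Protocol article, Clinical follow-up procedure).** An event counts if the patient has complaints identical to those before ablation and "the same type of narrow-complex tachycardia is recorded with any of the following: 12-lead ECG, Holter monitor or trans-telephonic event recorder (CardioMemo"). That is three sources, with no wording such as 'for example' or 'or equivalent'. There is one other route: "a recurrence is also identified in case the same type of clinical arrhythmia can be induced during a potential redo electrophysiology study", where that study was done because of recurrent palpitations.

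**How the further evidence is obtained (same section).** Recurrent symptoms lead to an extra visit with history and a 12-lead ECG. If judged necessary, "Holter monitoring (up to 3 weeks) and/or trans-telephonic event recorder (CardioMemo") can be added. The redo study is optional: "In the case of recurrence, a redo electrophysiology study can be scheduled". Table 2 lists neither telemetry nor device interrogation, and its footnote leaves the Holter and event-recorder decision to the treating cardiologist and the investigators jointly.

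**Use in the analysis (Protocol article, Statistical analysis).** "The recurrence rate of PSVT at 1 year (as an indicator of long-term success rate of the index procedure") is compared by chi-squared or Fisher's exact test and by logistic regression. In addition, "Freedom from PSVT recurrence will be determined with Kaplan–Meier analysis", with a log-rank test. Long-term success is a named secondary outcome.

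**The concern.** The protocol treats a strip or device recording as sound evidence of the arrhythmia before ablation, but gives it no weight afterwards and does not say why. Take a loop-recorder carrier who has the old complaints again at month five, with the same tachycardia stored by the device. On the text, that patient remains free of recurrence until something else captures the episode.

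Two errors can follow. If nothing else captures it, a recorded symptomatic recurrence is scored as one-year success and the patient is treated as event-free in the survival analysis. If a later Holter, event recorder or redo study does capture it, the event may carry too late a date, possibly beyond 12 months.

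The further capture depends on discretionary steps in an open-label trial. Few recurrences are expected, so a single one is visible in an arm's rate.

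**Working it through.** **1. The two lists side by side**

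| Source of recording | Accepted at entry | Accepted for recurrence |
|---|---|---|
| 12-lead ECG | yes | yes |
| Holter | yes | yes |
| Trans-telephonic recorder | yes | yes |
| Telemetry strip | yes | no |
| Implanted device (loop recorder, pacemaker) | yes | no |

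Induction at a redo study is a separate, optional route to recurrence. What is excluded is the recording, not the patient.

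**2. Who could be affected.** Carriers of a loop recorder or pacemaker at entry; patients who receive a pacemaker for AV block after ablation, which the adverse-event section lists as a possible complication; and patients with a strip from an unplanned hospital contact. The documents give no count for any of these.

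**3. The plan's own figure.** The sample size is built on the number of RF applications: log mean 1.39 against 1.043, SD 0.59, 80% power, two-sided 5%.
- Difference: 1.39 − 1.39 × 0.75 = 0.3475.
- n per arm = 2 × (1.960 + 0.842)² × 0.59² / 0.3475² ≈ 45.3, rounded up to 46; total 92, as stated.

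Recurrence does not enter this calculation, so the recurrence definition cannot affect it.

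**4. Expected recurrences.** The Background gives about 5% for AVNRT and about 8% for WPW-AVRT; the planned total is 112. The case mix is not given, so the two rates serve as bounds.
- 112 × 0.05 = 5.6
- 112 × 0.08 = 8.96

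That is about 6–9 events over both arms. On the 92 evaluable patients it would be 92 × 0.05 = 4.6 to 92 × 0.08 = 7.4.

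**5. Events missed.** Let *s* be the share of recurrences recorded only on a strip or device and not captured again. The documents do not give *s*; the range below is an assumption.

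Missed = 112 × rate × *s*; observed rate = rate × (1 − *s*).

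| *s* | Missed at 5% | Missed at 8% | 5% would read | 8% would read |
|---|---|---|---|---|
| 2% | 0.11 | 0.18 | 4.90% | 7.84% |
| 5% | 0.28 | 0.45 | 4.75% | 7.60% |
| 10% | 0.56 | 0.90 | 4.50% | 7.20% |
| 20% | 1.12 | 1.79 | 4.00% | 6.40% |

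**6. Weight of one event.** With 112 / 2 = 56 per arm, one uncounted event lowers that arm's rate by 1/56 = 1.8 percentage points. This is the effect of a single event if it happens, not an expected bias.

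**The case against.** The strongest defence is that the two lists do different jobs. At entry the recording is only one route to referral. Pre-excitation, or suggestive symptoms with no recording at all, also suffice, and every patient must then have AVNRT or WPW-AVRT identified at the EP study. No strip or device recording admits a patient by itself. An entry screen may be broader than an outcome definition, and nothing says the lists must match. This stands to the extent that the difference is not a contradiction in the protocol. It does not explain why a device recording that comes with identical symptoms and shows the same tachycardia should carry no weight.

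Second, there are backstops: the extra visit with ECG, Holter for up to three weeks, the event recorder and the redo study. An event is lost only if all of these miss it or are not used. This also stands, and it keeps the expected number small. It does not close the gap, because every step beyond the visit and its ECG is discretionary and a later capture can shift the event time.

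Third, the telemetry half is the weaker one. Patients go home within two days and no telemetry is scheduled, so only strips from unplanned care are in play.

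Fourth, a reader might infer that a few misclassified cases would change the comparison between arms. The documents do not support that. The rule is the same in both arms, and nothing suggests that device carriers cluster in one of them. At 56 per arm, Fisher's exact test gives p = 0.72 for 3 against 5 recurrences and p = 0.44 for 2 against 5. It crosses 5% only near complete separation, such as 0 against 6 (p = 0.027). The abstract's discussion already doubts that a significant gain in success rates can be shown.

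**Conclusion.** The discrepancy is on the face of the text, and it is a stated outcome rule rather than a detail left to a fuller document. A symptomatic recurrence recorded only on a telemetry strip or implanted device is not counted, or is counted late, unless it is captured again on an accepted recorder or induced at an optional redo study.

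One-year success and recurrence-free survival may therefore be slightly overstated in both arms. The size is unknown and probably small: about 0.1–1.8 of 6–9 expected recurrences, if 2–20% are affected. This rests on the protocol's 5–8% recurrence rates holding in this trial, on all 112 patients being followed, and on the assumed 2–20% share.

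It would go too far to say that long-term success is definitely overstated, since that depends on such events occurring and escaping the other routes. The primary endpoint and the sample size are unaffected. Severity: minor.

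**What to change.** In the recurrence definition, extend the accepted recordings to the sources already listed under Study population by adding the telemetry strip and the implanted device (loop recorder, pacemaker). Keep both existing conditions, identical complaints and the same type of tachycardia, so that incidental device detections do not count. Use only strips and device recordings that already exist, and apply the rule to both arms, including patients already in follow-up.

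Record the change as a dated amendment before the recurrence analysis, and report the results under the present definition as a sensitivity analysis. If the narrower list is intended, the protocol should instead give the reason.

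**Cost.** One sentence in the definition and one extra analysis, with no added visit, test or patient. There are three downsides:
- The reported recurrence rate may be slightly higher.
- A secondary outcome definition changes during an open-label trial, which is why the date and the sensitivity analysis matter.
- Device carriers will be ascertained somewhat more closely than other patients.
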